### Randomization

Eligible patients will be centrally randomized in a 1:1 ratio to the M-SCLI group and the E-SCLI group. Randomization will be stratified according to the following factors: neoadjuvant systemic therapy vs. adjuvant systemic therapy; T3-4 vs. T1-2; N3 vs. non-N3; ER positive vs. ER negative.

### Treatment arms

Trial participants will be allocated to two treatment groups:

M-SCLI group (standard arm): The radiation target volume includes ipsilateral medial SCL region, breast/chest wall, undissected axillary lymph nodes, and internal mammary nodes.E-SCLI group (experimental arm): The radiation target volume includes ipsilateral medial plus posterolateral SCL regions (also called entire SCL region), breast/chest wall, undissected axillary lymph nodes, and internal mammary nodes.

### Radiation therapy

#### Localization, simulation, and immobilization

Patients should be optimally positioned supine using breast boards, wing boards and/or other immobilization devices per treating physician’ discretion. Radio-opaque markers will be placed on the skin at scar, inframammary fold, and superior border of the breast tissue. A treatment planning CT scan will be performed with an image thickness of ≤ 0.5 cm.

#### Target and normal tissue volume definitions

##### Clinical target volumes (CTVs)

The CTVs include ipsilateral chest wall/breast, supraclavicular lymph nodes, undissected axilla (including interpectoral lymph nodes), and internal mammary nodes, with a tumor bed boost to the lumpectomy cavity for patients who underwent breast-conserving surgery. For patients who received mastectomy, a boost to the scar is delivered only when indicated. If positive internal mammary nodes are identified on initial CT and/or MRI, a nodal boost may be delivered at the discretion of the treating physician. In general, CTV delineation will follow the RTOG and ESTRO guidelines [7, 8, 18]. However, for some controversial areas, modifications have been made at Fudan University Shanghai Cancer Center to establish institutional guidelines for CTV delineation. The suggested CTV delineation for breast, chest wall, and lymph node regions is provided in Table 1.

**Table 1 Tab1:** Suggested CTV delineation for breast, chest wall, and lymph node regions

			Cranial	Caudal	Ventral	Dorsal	Medial	Lateral
Breast CTV (CTV_B)			Upper border of palpable/visible breast tissue; maximally up to the caudal edge of the sterno-clavicular joint	Most caudal CT slice with visible breast	5 mm under skin surface (3 mm for small breast)	Major pectoral muscle or costae and intercostal muscles where no muscle	Lateral to the medial perforating mammarian vessels; maximally to the edge of the sternal bone	Lateral breast fold; anterior to the lateral thoracic artery
Chest wall CTV (CTV_CW)			Guided by palpable/visible signs; if appropriate guided by the contralateral breast; maximally up to the caudal edge of the sterno-clavicular joint	Guided by palpable/visible signs; if appropriate guided by the contralateral breast	Skin	Major pectoral muscle or costae and intercostal muscles where no muscle (For T4a/T4c cases, the major pectoral muscle and ribs should be included)	Guided by palpable/visible signs; if appropriate guided by the contralateral breast	Guided by palpable/visible signs; if appropriate guided by the contralateral breast. Usually anterior to the mid-axillary line
Supraclavicular CTV	Medial supraclavicular CTV (CTV_M_SCL)		Caudal to the cricoid cartilage	Includes the subclavian vein with 5 mm margin, thus connecting to the cranial border of CTVn_IMN	Sternocleidomastoid muscle, dorsal edge of the clavicle	Anterior aspect of the scalene muscle	Including the jugular vein without margin; excluding the thyroid gland and the common carotid artery	Cranial: Sternocleidomastoid muscle Caudal: junction of 1st rib and clavicle
	Entire supraclavicular CTV (CTV_E_SCL)		Same as above	Same as above	Same as above	Trapezius muscle	The same as CTV_M_SCL anteriorly, avoids the scalene and elevator scapulae muscles posteriorly	Sternocleidomastoid muscle, clavicle, and connecting to axillary level III
Internal mammary node CTV (CTV_IMN)			Caudal limit of CTV_SCL	Cranial side of the 4th rib (in selected cases 5-6th rib)	Ventral limit of the vascular area	Pleura	5 mm from the internal mammary vein (artery in cranial part down to and including first intercostal space)	5 mm from the internal mammary artery
Undissected axillary CTV (CTV_udALN)		Undissected Axillary level 2	Includes the cranial extent of the axillary artery (i.e. 5 mm cranial of axillary vein)	The caudal border of the minor pectoral muscle, but should exclude the extent of the dissection	Minor pectoral muscle	Up to 5 mm dorsal of axillary vein or to costae and intercostal muscles	Medial edge of minor pectoral muscle	Lateral edge of minor pectoral muscle, but should exclude the extent of the dissection
		Axillary level 3	Includes the cranial extent of the subclavian artery (i.e. 5 mm cranial of subclavian vein)	5 mm caudal to the subclavian vein	Major pectoral muscle	Same as level 2	Junction of subclavian and internal jugular veins, connects to CTV_SCN	Medial side of the minor pectoral muscle
		Interpectoral nodes	Includes the cranial extent of the axillary artery (i.e. 5 mm cranial of axillary vein)	The caudal border of the minor pectoral muscle	Major pectoral muscle	Minor pectoral muscle	Medial edge of minor pectoral muscle	Lateral edge of minor pectoral muscle

Abbreviations: CTV=clinical target volume; CT=computer tomography

*Tumor bed (TB)*: Contoured using all available clinical and radiographic information, including surgical clips, excision cavity volume, seroma, architectural distortion, lumpectomy scar.*Tumor bed CTV (CTV_TB)*: Defined as 1 cm 3D expansion around the TB. Limit dorsal border at anterior surface of the pectoralis and/or serratus anterior muscles, and ventral border at 5 mm under skin surface.*Breast CTV (CTV_B)*: Same as the definitions of the ESTRO breast cancer consensus guidelines.*Chestwall CTV (CTV_CW)*: Same as the definitions of the ESTRO breast cancer consensus guidelines, except for the ventral border is skin due to thin postoperative chest wall in Chinese patients. For T4a/T4c cases, the major pectoral muscle and ribs should be included. The surgical scar is routinely included in the CTV_CW.*Supraclavicular CTV*.* Medial supraclavicular CTV (CTV_M_SCL)*: Follows the definitions of RTOG or ESTRO breast cancer consensus guidelines. The cranial border is caudal to the cricoid cartilage; the caudal border is the junction of the internal jugular vein and subclavian vein; the ventral border is sternocleidomastoid muscle and dorsal edge of the clavicle; the dorsal border is anterior aspect of the scalene muscle (anterior and medial); the medial border includes the internal jugular vein and excludes the thyroid gland and the common carotid artery; the lateral border is sternocleidomastoid muscle (cranial), junction of the first rib and clavicle (caudal). The atlas of CTV_M_SCL is shown in Fig. 2A.*Entire supraclavicular CTV (CTV_E_SCL)*: The cranial, caudal, and ventral borders are the same as the definitions of CTV_M_SCL. The dorsal border is trapezius muscle; the medial border is the same as CTV_M_SCL anteriorly, avoids the scalene and elevator scapulae muscles posteriorly; the lateral border is sternocleidomastoid muscle, clavicle, and connecting to axillary level III. The atlas of CTV_E_SCL is shown in Fig. 2B.*Internal mammary node CTV (CTV_IMN)*: Same as the definitions of the ESTRO breast cancer consensus guidelines, including the internal mammary vessels in the first three intercostal spaces. The caudal limit of CTV_IMN is typically the cranial side of the 4th rib, but might be individually extended by one or two more intercostal space per treating physician’ discretion for patients with metastatic internal mammary nodes or based on tumor location and burden.*Undissected axillary CTV (CTV_udALN)*: Since axillary dissection typically removes level 1–2 axillary nodes. CTV_udALN consists of the undissected portions of axilla, typically including level 3, some of axillary level 2, and interpectoral nodes. The caudal and lateral borders are the most cranial and medial extent of the dissection, other anatomical borders follow the definitions of the ESTRO breast cancer consensus guidelines for axillary levels.

**Fig. 2 Fig2:**
[figure not shown]
Atlas of medial supraclavicular CTV (CTV_M_SCL) and entire supraclavicular CTV (CTV_E_SCL). **A**: CTV_M_SCL (red). **B**: CTV_E_SCL (red). Abbreviations: CTV = clinical target volume

##### Planning target volumes (PTVs)

PTVs are generated by adding 5 mm uniform margins to the CTVs, including PTV_TB, PTV_B, PTV_CW, PTV_SCL, PTV_IMN, and PTV_unALN. For patients who underwent breast-conserving surgery, additional PTV_B_EVA and PTV_TB_EVA are generated by limiting the ventral border of PTV_B and PTV_TB at 5 mm beneath the skin surface for dose volume histogram (DVH) evaluation. Similarly, for patients who underwent mastectomy, an additional PTV_CW_EVA is generated by limiting the ventral border of PTV_CW at skin surface for DVH evaluation.

##### Organs at risk (OARs)

Normal structures include heart, left anterior descending, ipsilateral lung, contralateral lung, contralateral breast, humeral head, thyroid, esophagus, and brachial plexus. Of these structures, left anterior descending are optional.

#### Dose specifications

Both hypofractionated and conventional fractionated radiation therapy are permitted: the conventional fractionated regimen is 50 Gy in 25 fractions of 2 Gy; the hypofractionated schedule is 42.5 Gy in 16 fractions of 2.67 Gy. Tumor bed or scar boost is at the discretion of the treating physician, boost doses will be 10 ~ 16 Gy in 5 ~ 8 fractions of 2 Gy, for total cumulative doses of 60 ~ 66 Gy.

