#### Technique factors and treatment planning

3D-conformal radiation therapy (3D-CRT) techniques are not recommended due to significant incidental irradiation of the SCL region. Advanced intensity modulated radiation therapy (IMRT), volumetric modulated arc therapy (VMAT), or tomotherapy techniques are recommended instead. Methods to minimize the cardiac exposure such as gating or breath-holding are permitted per treating physician’ discretion.

Suggested PTV compliance criteria are as follows: at least 95% of each PTV receives ≥ 95% of the prescribed dose (it is acceptable if ≥ 95% of each PTV receives ≥ 90% of the prescribed dose, except for PTV_IMN, it is acceptable if ≥ 90% of the PTV_IMN receives ≥ 90% of the prescribed dose); the maximum point dose (volume that is 0.03 cm^3^) is recommended to be ≤ 115% of the prescription dose (≤ 120% acceptable), and should be evaluated without the contribution of the boost fields; ≤ 35% of the PTV_B_EVA, PTV_CW_EVA, or PTV_IMN receives 100% of the boost prescribed dose when a boost is included in the composite plan (≤ 40% acceptable); ≤ 5% of the PTV_TB_EVA receives ≥ 110% of the boost prescribed dose (≤ 10% acceptable).

The OARs dose constraints are shown in Table 2.

**Table 2 Tab2:** Suggested dose constraints of organs at risk

	Conventional fractionated RT (50 Gy in 25 fractions)		Hypofractionated RT (42.56 Gy in 16 fractions)	
	required	acceptable	required	acceptable
Heart(Left_sided)	Dmean ≦ 6 Gy	Dmean ≦ 8 Gy	Dmean ≦ 5.1 Gy	Dmean ≦ 6.8 Gy
	V20Gy ≦ 5%	V25Gy ≦ 5%	V17Gy ≦ 5%	V21Gy ≦ 5%
Heart(Right_sided)	Dmean ≦ 2 Gy	Dmean ≦ 3 Gy	Dmean ≦ 1.7 Gy	Dmean ≦ 2.6 Gy
	V20Gy ≦ 0%	V25Gy ≦ 0%	V17Gy ≦ 0%	V21Gy ≦ 0%
Ipsilateral Lung	V20Gy ≦ 30%	V20Gy ≦ 35%	V17Gy ≦ 30%	V17Gy ≦ 35%
	V5Gy ≦ 60%	V5Gy ≦ 70%	V4.2 Gy ≦ 60%	V4.2 Gy ≦ 70%
Contralateral lung	V5Gy ≦ 10%	V5Gy ≦ 15%	V4.2 Gy ≦ 10%	V4.2 Gy ≦ 15%
Contralateral breast	V5Gy ≦ 10%	V5Gy ≦ 15%	V4.2 Gy ≦ 10%	V4.2 Gy ≦ 15%
Thyroid	Dmean ≦ 25 Gy	Dmean ≦ 26.2 Gy	Dmean ≦ 21.2 Gy	Dmean ≦ 22.2 Gy
Esophagus	V20Gy ≦ 10%	V20Gy ≦ 15%	V17Gy ≦ 10%	V17Gy ≦ 15%
Spinal cord	Dmax ≦ 45 Gy		Dmax ≦ 38.2 Gy	
Humeral head	Dmean ≦ 25 Gy	Dmean ≦ 26.2 Gy	Dmean ≦ 21.2 Gy	Dmean ≦ 22.2 Gy
	V30Gy ≦ 30%	V30Gy ≦ 35%	V28.5 Gy ≦ 30%	V28.5 Gy ≦ 35%
Brachial plexus	Dmax ≦ 54 Gy	Dmax ≦ 56.7 Gy	Dmax ≦ 46 Gy	Dmax ≦ 48.3 Gy

V_XXGy_ ≦YY%: the volume of each organs at risk receiving XXGy should be no more than YY%

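### The single cumulative boost range of 60–66 Gy follows only from the 50 Gy schedule; on the hypofractionated schedule the stated boost reaches about 52.5–58.7 Gy

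*Protocol article*

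**What the plan says.** Dose specifications in the protocol article opens by allowing two schedules: "Both hypofractionated and conventional fractionated radiation therapy are permitted". The first is defined as follows: "the conventional fractionated regimen is 50 Gy in 25 fractions of 2 Gy". For the second, "the hypofractionated schedule is 42.5 Gy in 16 fractions of 2.67 Gy".

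A tumor bed or scar boost is left to the treating physician, and its size is then fixed: "boost doses will be 10 ~ 16 Gy in 5 ~ 8 fractions of 2 Gy", "for total cumulative doses of 60 ~ 66 Gy". Neither the boost nor the cumulative range is restricted to one schedule, and nothing in the article describes the range as a biologically equivalent dose.

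Table 2, under Technique factors and treatment planning, heads its hypofractionated columns "Hypofractionated RT (42.56 Gy in 16 fractions", a different total from the one in the text.

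**The concern.** One boost rule and one cumulative total are attached to two schedules whose base doses differ by more than 7 Gy. Both cannot be right as physical sums for both schedules. For a hypofractionated patient who is to be boosted, the boost clause and the cumulative clause give different answers.

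This is a treatment specification in a multicenter trial that, according to Trial status, is still accruing. Boosts are not a rarity: the section on clinical target volumes includes a tumor bed boost after breast-conserving surgery. The suggested planning limits for composite plans also refer to the boost prescription. If that means the cumulative total, which the article does not say, the reference dose is unclear by the same amount.

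The second, smaller matter is that the hypofractionated total, its fraction size and the Table 2 header do not agree with one another.

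**Working it through.** **Inputs.** All are from Dose specifications except the last.
- Conventional: 25 fractions × 2 Gy, stated total 50 Gy.
- Hypofractionated: 16 fractions × 2.67 Gy, stated total 42.5 Gy.
- Boost: 5–8 fractions × 2 Gy, stated as 10–16 Gy.
- Cumulative dose with boost: 60–66 Gy.
- Table 2 header: 42.56 Gy in 16 fractions.

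**Formulas.** Total = fractions × dose per fraction. Cumulative = base total + boost.

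**Step 1: reproduce the stated range.** 25 × 2 = 50 Gy. The boost is 5 × 2 = 10 to 8 × 2 = 16 Gy. 50 + 10 = 60 and 50 + 16 = 66. The range is reproduced exactly for the conventional schedule.

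**Step 2: apply the same boost to the hypofractionated schedule.** The article supports three values of the base total: the text total, the Table 2 total, and the product 16 × 2.67.

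| Base total (Gy) | Per fraction (Gy) | + 10 Gy | + 16 Gy | Short of 60 and of 66 by | Boost needed for 60–66 | In 2 Gy fractions |
|---|---|---|---|---|---|---|
| 42.50 (text) | 2.656 | 52.50 | 58.50 | 7.50 | 17.50–23.50 | 8.75–11.75 |
| 42.56 (Table 2) | 2.66 | 52.56 | 58.56 | 7.44 | 17.44–23.44 | 8.72–11.72 |
| 42.72 (16 × 2.67) | 2.67 | 52.72 | 58.72 | 7.28 | 17.28–23.28 | 8.64–11.64 |

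The highest reachable total, 58.72 Gy, is below the 60 Gy floor, so the reachable and stated ranges do not overlap. Even the smallest boost that would reach 60 Gy (17.28 Gy, at least 9 whole fractions of 2 Gy) exceeds both the 16 Gy and the 8-fraction limits.

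**Step 3: does a 2-Gy-equivalent reading rescue the range?** The article gives no conversion and no α/β, so this step rests on an assumption. With d = base total / 16 and an assumed α/β of r, the equivalent base dose is total × (d + r)/(2 + r). For 42.5 Gy and r = 3: 42.5 × (2.656 + 3)/(2 + 3) = 48.08 Gy, giving 58.08–64.08 Gy with the boost. Across the three base totals:

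| Assumed α/β (Gy) | With 10 Gy boost | With 16 Gy boost |
|---|---|---|
| 1.5 | 60.47–60.90 | 66.47–66.90 |
| 2 | 59.47–59.88 | 65.47–65.88 |
| 3 | 58.08–58.44 | 64.08–64.44 |
| 4 | 57.15–57.49 | 63.15–63.49 |
| 10 | 54.82–55.11 | 60.82–61.11 |

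The stated range is approached only for an assumed α/β of about 2 or less. Since it is also the exact physical sum for the 50 Gy schedule, the simpler explanation is that it was written for that schedule and not qualified.

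**Step 4: consistency of the hypofractionated prescription.** 16 × 2.67 = 42.72, not 42.5. 42.5/16 = 2.656. 42.56/16 = 2.66. The 42.5 in the text could be 42.56 rounded, but 2.67 fits neither total. The spread is 42.72 − 42.50 = 0.22 Gy, and 0.22/42.5 is about 0.5%.

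**The case against.** The arithmetic is not in dispute. The case on the other side concerns consequences, and most of it stands.

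- **Different centers treating the same patient differently.** A reader might infer that some centers follow the boost range and others the cumulative total, and that patients have been affected. The article does not support this. It fixes the boost by dose, fraction number and fraction size, while the cumulative range reads as a trailing result. A center can comply with all three boost figures on either schedule, and only the total then fails. Reaching the total would mean breaking both the dose and the fraction limits, so the two readings are not equally likely in practice. That is a judgement about how the text would be read, not about which figure is right.
- **Effect on plan criteria and Table 2.** A reader might infer that the unsettled hypofractionated total undermines these. It does not to any visible degree. The Table 2 limits are absolute doses and volumes at fixed dose levels, and they do not move with the header. The 115% maximum-dose criterion is assessed without the boost fields. A 0.5% spread is small beside a 95% coverage target with 90% acceptable. Only two totals are printed; the third is a product of printed figures.
- **Bias in the endpoints.** A reader might infer that the comparison is distorted. The boost targets tumor bed or scar (or, at discretion, a positive internal mammary node), not the supraclavicular volume being compared. Other volumes are the same in both arms and allocation is randomized 1:1, so any ambiguity is expected to fall equally on both. The article gives no counts of hypofractionated or boosted patients, so the size of any added heterogeneity is unknown.
- **This is a condensed article.** The full protocol may be correct, so a failure at sites cannot be inferred. Condensation explains omissions, however, and this is a stated range that is wrong for one of the two permitted schedules. The contradiction itself remains.

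**Conclusion.** The point holds as an internal contradiction in a treatment specification. The 60–66 Gy range follows only from the 50 Gy schedule. On the hypofractionated schedule the stated boost gives about 52.5–58.7 Gy, 7.3–7.5 Gy short at each end, and the stated total cannot be met within the stated boost dose and fraction limits. This rests on reading the doses as physical sums, which is how the article presents them. A 2-Gy-equivalent reading is not stated and would need an assumed α/β of about 2 or less.

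The mismatch between 42.5 Gy, 16 × 2.67 Gy and 42.56 Gy is real but minor, about 0.5%, with little practical effect on plan acceptance.

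The boost contradiction reaches only patients who are both hypofractionated and boosted. Neither between-arm bias nor actual mistreatment is shown. It still deserves correction, because it is a dose instruction that one permitted group cannot follow in full as written.

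**What to change.** Reconcile Dose specifications with Table 2 so that the hypofractionated total, the fraction size and the table header agree and multiply out. State the boost and cumulative dose separately for each schedule, or limit the cumulative range to the schedule it applies to. If an equivalent dose was meant, say so and give the conversion. All values are for the clinical team to decide.

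Check whether the full protocol carries the same text. If it does, issue a clarification to sites; if not, a correction to the article is enough. The cost is a short text change and possibly a letter to sites, with no effect on sample size or analysis.

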#### Technique factors and treatment planning

3D-conformal radiation therapy (3D-CRT) techniques are not recommended due to significant incidental irradiation of the SCL region. Advanced intensity modulated radiation therapy (IMRT), volumetric modulated arc therapy (VMAT), or tomotherapy techniques are recommended instead. Methods to minimize the cardiac exposure such as gating or breath-holding are permitted per treating physician’ discretion.

Suggested PTV compliance criteria are as follows: at least 95% of each PTV receives ≥ 95% of the prescribed dose (it is acceptable if ≥ 95% of each PTV receives ≥ 90% of the prescribed dose, except for PTV_IMN, it is acceptable if ≥ 90% of the PTV_IMN receives ≥ 90% of the prescribed dose); the maximum point dose (volume that is 0.03 cm^3^) is recommended to be ≤ 115% of the prescription dose (≤ 120% acceptable), and should be evaluated without the contribution of the boost fields; ≤ 35% of the PTV_B_EVA, PTV_CW_EVA, or PTV_IMN receives 100% of the boost prescribed dose when a boost is included in the composite plan (≤ 40% acceptable); ≤ 5% of the PTV_TB_EVA receives ≥ 110% of the boost prescribed dose (≤ 10% acceptable).

The OARs dose constraints are shown in Table 2.

**Table 2 Tab2:** Suggested dose constraints of organs at risk

	Conventional fractionated RT (50 Gy in 25 fractions)		Hypofractionated RT (42.56 Gy in 16 fractions)	
	required	acceptable	required	acceptable
Heart(Left_sided)	Dmean ≦ 6 Gy	Dmean ≦ 8 Gy	Dmean ≦ 5.1 Gy	Dmean ≦ 6.8 Gy
	V20Gy ≦ 5%	V25Gy ≦ 5%	V17Gy ≦ 5%	V21Gy ≦ 5%
Heart(Right_sided)	Dmean ≦ 2 Gy	Dmean ≦ 3 Gy	Dmean ≦ 1.7 Gy	Dmean ≦ 2.6 Gy
	V20Gy ≦ 0%	V25Gy ≦ 0%	V17Gy ≦ 0%	V21Gy ≦ 0%
Ipsilateral Lung	V20Gy ≦ 30%	V20Gy ≦ 35%	V17Gy ≦ 30%	V17Gy ≦ 35%
	V5Gy ≦ 60%	V5Gy ≦ 70%	V4.2 Gy ≦ 60%	V4.2 Gy ≦ 70%
Contralateral lung	V5Gy ≦ 10%	V5Gy ≦ 15%	V4.2 Gy ≦ 10%	V4.2 Gy ≦ 15%
Contralateral breast	V5Gy ≦ 10%	V5Gy ≦ 15%	V4.2 Gy ≦ 10%	V4.2 Gy ≦ 15%
Thyroid	Dmean ≦ 25 Gy	Dmean ≦ 26.2 Gy	Dmean ≦ 21.2 Gy	Dmean ≦ 22.2 Gy
Esophagus	V20Gy ≦ 10%	V20Gy ≦ 15%	V17Gy ≦ 10%	V17Gy ≦ 15%
Spinal cord	Dmax ≦ 45 Gy		Dmax ≦ 38.2 Gy	
Humeral head	Dmean ≦ 25 Gy	Dmean ≦ 26.2 Gy	Dmean ≦ 21.2 Gy	Dmean ≦ 22.2 Gy
	V30Gy ≦ 30%	V30Gy ≦ 35%	V28.5 Gy ≦ 30%	V28.5 Gy ≦ 35%
Brachial plexus	Dmax ≦ 54 Gy	Dmax ≦ 56.7 Gy	Dmax ≦ 46 Gy	Dmax ≦ 48.3 Gy

V_XXGy_ ≦YY%: the volume of each organs at risk receiving XXGy should be no more than YY%

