**Methods:**

The SUCLANODE trial is an open-label, multicenter, randomized, phase 3 trial comparing the efficacy and adverse events of medial SCL irradiation (M-SCLI group) and medial plus posterolateral SCL irradiation (entire SCL irradiation, E-SCLI group) in high-risk breast cancer patients who underwent breast conserving-surgery or mastectomy. Patients with pathological N2-3b disease following initial surgery, or clinical stage III or pathological N1-3b if receiving neoadjuvant systemic therapy, are eligible and randomly assigned (1:1) to M-SCLI group and E-SCLI group. Stratification is by chemotherapy sequence (neoadjuvant vs. adjuvant), T stage (T3-4 vs. T1-2), N stage (N1-2 vs. N3), and ER status (positive vs. negative). Other radiation volumes are identical in the two arms, including breast/chest wall, undissected axillary lymph node, and internal mammary node. Advanced intensity modulated radiation therapy (IMRT), volumetric modulated arc therapy (VMAT), or tomotherapy techniques are recommended. Both hypofractionated and conventional fractionation schedules are permitted. The primary end point is invasive disease-free survival, and secondary end points included overall survival, SCL recurrence, local-regional recurrence, distance recurrence, safety outcome, and patient-reported outcomes. The target sample size is 1650 participants.

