#### Treatment verification

Before the first time of radiotherapy, portal films or 3D-CRT images (e.g., conebeam CT, MV CT, kV CT) must be obtained and approved by a physician. During radiotherapy, portal films or 3D-CRT images must be obtained every 5 fractions.

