### Sample size and statistical analysis

The primary endpoint is DFS. According to data from a Chinese prospective study, the 5-year DFS for high-risk patients after breast-conserving surgery or mastectomy is 73% [19] (control group). We assume a clinically meaningful difference in 5-year DFS of 5% between groups. The hypothesis of the current study is that the 5-year DFS will be superior in the E-SCLI group (experiment group) compared to the M-SCLI group (control group), with a 5-year DFS increase from 73% in the M-SCLI group to 78% in the E-SCLI group. Sample size calculation for comparing DFS was performed with a two-sided α = 0.05 and 80% power. Hazard ratio is 0.79. This yields to a total sample size of 1500 patients. Accounting for a 10% dropout rate, the total sample size is increased to 1650 patients (825 per group). Based on these assumptions, it is estimated that 510 events will be required for the final analysis. Statistical analysis will be performed based on the intent-to-treat principle, with all patients analyzed as randomized, regardless of eligibility or protocol compliance.

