The biophysical effects of radiotherapy are not tumor-specific and can also cause toxicity due to exposure of surrounding normal tissues. The toxicity is of particular concern in breast cancer as more patients become long-term survivors due to advances in systemic and local therapies. Expanding the SCL target volume will inevitably increase neck and shoulder radiation dose, potentially heightening acute and late normal tissue toxicity and reducing quality of life. Bazan et al. found 3D-CRT technique delivered significantly higher incidental dose to the shoulder and back versus IMRT technique, with a tend toward reduced q-DASH scores indicating less shoulder morbidity in patients treated with IMRT technique (*p* = 0.078) [20]. Our prior study also observed a significantly higher rate of pain in the E-SCLI group compared to M-SCLI (26.6% vs. 15.1%, *p* = 0.005) [17]. In this trial, we will evaluate shoulder function via q-DASH questionnaire, patients-reported shoulder/back symptoms, and quality of life. Additionally, a previous study showed 3D-CRT technique delivered significantly higher incidental radiation dose to the posterolateral SCL region than IMRT technique (46.7 Gy vs. 30.2 Gy *P* < 0.0001) when treating medial SCL region based on RTOG consensus [20]. We will utilize advanced IMRT, VMAT, or tomotherapy techniques instead of 3D-CRT technique to minimize incidental irradiation to the posterolateral SCL region in the M-SCLI arm.

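### The technique rule should be as firm as the stated intent: the Methods only discourage 3D-CRT, while the Discussion says it will be replaced to limit posterolateral dose in the control arm

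*Protocol article*

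**What the plan says.** The technique rule appears in three places in the protocol article.

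- Technique factors and treatment planning (Methods): "3D-conformal radiation therapy (3D-CRT) techniques are not recommended due to significant incidental irradiation of the SCL region". The next sentence recommends IMRT, VMAT or tomotherapy in its place.
- Abstract, Methods: "Advanced intensity modulated radiation therapy (IMRT), volumetric modulated arc therapy (VMAT), or tomotherapy techniques are recommended". 3D-CRT is not mentioned there.
- Discussion: "We will utilize advanced IMRT, VMAT, or tomotherapy techniques instead of 3D-CRT technique to minimize incidental irradiation". The sentence goes on to make clear that it means dose reaching the posterolateral area in control patients. The reason given just before is a previous study in which, with only the medial region targeted, 3D-CRT delivered "significantly higher incidental radiation dose to the posterolateral SCL region than IMRT technique (46.7 Gy vs. 30.2 Gy").

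Two other statements bear on the point. The Abstract says of the design: "Other radiation volumes are identical in the two arms". Sample size and statistical analysis specifies intention to treat, "with all patients analyzed as randomized, regardless of eligibility or protocol compliance".

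**The concern.** The first two statements are advice and the third is a commitment. No section of the article prohibits 3D-CRT. Neither the target coverage criteria nor the organ-at-risk constraints in Table 2 cap posterolateral SCL dose in the M-SCLI arm. A site that follows the Methods text could therefore plan a control patient with 3D-CRT and stay within the printed rules.

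This falls on the one region where the arms are meant to differ. A control patient planned with 3D-CRT would move towards the experimental arm in that region. The intention-to-treat analysis is the right one, but it keeps such a patient in the control arm and cannot restore the lost contrast. Only the planning rule can prevent the problem.

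The toxicity comparison is exposed in the same way. The Background singles out shoulder function and pain, and the Discussion reports higher incidental shoulder and back dose with 3D-CRT than with IMRT.

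**Working it through.** The point is mainly textual. The plan states no figure that needs to be reproduced for it.

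**Force of each statement**

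| Place | IMRT, VMAT or tomotherapy | 3D-CRT |
|---|---|---|
| Abstract, Methods | recommended | not mentioned |
| Technique factors and treatment planning | recommended | discouraged, not prohibited |
| Discussion | will be used | will be replaced |

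All three point the same way. They differ in strength, and the weakest wording is in the section that a site would follow when planning.

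**Size of the dose difference at stake** (both inputs from the Discussion, medial-only targeting)

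- 3D-CRT: 46.7 Gy to the posterolateral SCL region
- IMRT: 30.2 Gy
- Difference: 46.7 − 30.2 = 16.5 Gy
- Ratio: 46.7 / 30.2 = 1.55

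**How far those figures transfer**

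The cited study contoured to the RTOG consensus. This trial's medial volume follows RTOG or ESTRO definitions (Clinical target volumes). Its dorsal border, the anterior aspect of the scalene muscle, is the one that the Background attributes to RTOG. The figures are therefore relevant, but they are not this trial's own. The article does not give the cited study's prescription, and this trial also allows a 16-fraction schedule (Dose specifications). For that reason the doses are not expressed here as percentages of 50 Gy.

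**What cannot be calculated**

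A power loss would need two inputs: the share of M-SCLI patients planned with 3D-CRT, and the effect of incidental posterolateral dose on disease-free survival. The article gives neither.

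**The case against.** The strongest reply is that nothing here is wrong. The article names the hazard, steers sites away from 3D-CRT and explains why, so only the strength of the wording differs. Advisory language is also the normal register of the planning text: the target volumes, the coverage criteria and the organ dose limits are all presented as suggestions. The Treatment verification section does use mandatory wording, "portal films or 3D-CRT images (e.g., conebeam CT, MV CT, kV CT) must be obtained and approved by a physician", but that one rule on imaging does not show that 3D-CRT treatment is acceptable. This stands, and it is why the point is an improvement and not an error.

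The article's own evidence also gives little ground for expecting an effect on outcome. The Discussion reports posterolateral SCL recurrence in 2 of 544 patients in the earlier retrospective series, one of them in-field after entire SCL irradiation. In a second series it reports 1 of 268, in a patient treated with 3D-CRT whose mean dose to that region was 4647 cGy. It infers that such recurrences may not be due to inadequate coverage. This stands as well.

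Three stronger readings are tempting, and the document supports none of them:

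- **The article contradicts itself.** It does not. A recommendation and a stated intention in the same direction are compatible.
- **Control patients are being treated with 3D-CRT.** Nothing in the article says so.
- **The trial loses a definable amount of power.** Any such figure would have to assume both the 3D-CRT share and that those controls receive the full experimental benefit.

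It can also be said that an article leaves detail to the full protocol. That covers deviation logging and plan-dose reporting, which are not pressed here. It does not cover the strength of the technique rule, which the article states itself, twice as advice and once as a commitment.

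**Conclusion.** The point holds as a specific, low-cost improvement. The printed technique rule is weaker than the intent stated for it, and the gap concerns the only region where the arms are planned to differ. Its size is bounded by the cited comparison: 16.5 Gy more to the posterolateral region for each control planned with 3D-CRT instead of IMRT, if those external doses carry over to this trial. How many patients this affects is unknown, and so is any consequence for disease-free survival.

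A firm rule would reduce incidental dose but not remove it, because IMRT still delivered 30.2 Gy in the cited study. The full protocol is not shown. If it already requires IMRT, VMAT or tomotherapy, the article's wording is all that needs to change.

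**What to change.** In Technique factors and treatment planning, state that IMRT, VMAT or tomotherapy is required in both arms and that 3D-CRT is not permitted for patients still to be planned. Align the Abstract. Keep all patients in the intention-to-treat analysis, and report the number treated with 3D-CRT by arm, including those already treated.

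**Cost.** The change is wording in two places, a record of technique for each patient and one count per arm in the report. Accrual began on September 1, 2021, so the rule can bind only future plans; for earlier patients only the count is available. The real downside is that sites or patients limited to 3D-CRT could not take part.

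Two related items are optional and not part of this point. The Treatment verification section labels cone-beam, MV and kV CT as 3D-CRT images, a clerical matter that could be tidied in the same edit. Where stored plans allow, mean dose to the posterolateral region (the entire SCL volume minus the medial volume) could be reported by arm to help interpret a null result.
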